### Patient and Public Involvement

The design of this study was informed by PPI through a self-harm in young people PPI advisory group, including young people and carers, led by the CI at Keele University, and by consulting the McPin Foundation’s Young People’s Advisory Group and the Kings College London/NIHR Maudsley Biomedical Research Centre Young Person’s Mental Health Advisory Group. This feasibility study will be supported by the COPING study PPI advisory group consisting of five young people who self-harm and three carers of young people who self-harm. This group contributed to the design of COPING by generating ideas for consideration in co-production activities in the COPING-ID study.

The first study meeting occurred on 9 May 2023 where all members of the advisory group attended, and the group helped design the participant eligibility and study progression criteria. Members also gave feedback about the content and design of the participant study information sheet and participant recruitment poster. The group will meet two monthly to support the delivery and dissemination of this study.

### Data collection methods

Patients who consent to participate will be asked to complete an online baseline questionnaire which will collect data on participant age, sex, ethnicity, medication, number and time of recent self-harm episodes, the patient health questionnaire (PHQ-9), the Suicidal Behaviours Questionnaire-Revised (SBQ-R), and educational status.

Participant follow-up outcome data collection will be at eight weeks, four, and six months, from baseline using a self-report electronic questionnaire. Data collected will include individual participant repetition of self-harm via the SBQ-R, and PHQ-9 scores will be attained at these timepoints. Participants will be asked if they would be willing to be randomised in a future RCT of COPING in the eight-week follow-up questionnaire. One email or SMS text message reminder will be sent after one week if there has been no response after each questionnaire invitation. If a participant withdraws from the study, their data will be retained and used for the study. In the situation a participant withdraws from completing the COPING treatment, they will still be invited to complete the follow-up questionnaires.

GPs will record training time, length of COPING consultations, and attendance of participant at 2nd COPING consult on Case Report Forms (CRF). General practice medical records of participants will be reviewed and relevant aspects extracted and depersonalised at participant sites, and securely transferred to the study team to obtain information for example about past medical history and prescriptions.

GPs around England will be invited to complete an online survey. This survey will ask GPs about the number of self-harm presentations in young people 16–25 years they see each month; willingness to be involved in a future RCT, including being randomised; barriers and enablers to COPING implementation; and likelihood of contamination in a future individually randomised RCT.

### Statistical methods

Participant characteristics, eligibility and recruitment rates, attendance at second COPING consult, baseline and follow-up questionnaire response rates, GP survey responses, and resource use will be reported descriptively using SPSS (Statistical Package for the Social Sciences) v27 or later
^
30
^. Continuous variables (e.g., age) will be reported with means and standard deviations or median (IQR) as appropriate and categorical variables (e.g., sex) will be reported with frequencies and percentages.

Analysis of outcomes against the predefined feasibility study progression criteria will include estimated percentages with 95% confidence intervals (e.g., rates of consent or willingness to be randomised). Participant follow-up rate of outcome measures will be assessed as the total completions attained of the SBQ-R measure at all three timepoints as a percentage of the possible denominator (n=93). Participant adherence to the COPING intervention will be ascertained by examining the proportion of participants who attend for the 2nd COPING consult. Participant PHQ-9 and SBQ-R scores at baseline and follow-up timepoints will be compared using paired t-test (if normal distribution) or Wilcoxon paired rank test
^
31
^.

Fidelity of the COPING intervention will be measured retrospectively by reviewing CRF data completed by site GPs against the COPING delivery checklist. Overall fidelity will be calculated as a percentage of the participants where the number of COPING items successfully delivered is at least three out of five (from the five BCTs targeting the young person’s target behaviour), as agreed with the SSC.

We will investigate how much missing data there is in this study to inform the planning of a future RCT. This will occur at two levels: i) observe how much loss to follow-up there will be (participant attrition or withdrawal), and ii) assess completion rates, including missing data for specific data items, of follow-up questionnaires.

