## Methods

### Study design

This study is a mixed-methods external non-randomised before-after single arm feasibility study.

This study is registered on ISRCTN registry, 28.11.2023: ISRCTN16572400;
https://www.isrctn.com/ISRCTN16572400.

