### Eligibility criteria

Patients will be eligible to participate if they are aged 16–25 years and have self-harmed (according to the definition of the National Institute for Health and Care Excellence) in the last 12 months
^
1
^. Exclusion criteria include acute risk of suicide or harm to others necessitating urgent referral/admission; moderate to severe learning disabilities; current psychotic episode or organic mental illness; receiving current psychological therapy; patient inappropriate for COPING at clinician discretion; and lacking capacity for informed consent.

At general practice study sites, GPs will be eligible to deliver COPING if they complete the site COPING training.

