### Outcomes

The primary outcomes are:

- Consent to study of eligible patients- Young people participants willing to be randomised in a main RCT- Fidelity to COPING- Participant adherence to COPING- Participant follow-up rate of outcome measures- Acceptability of COPING to participants and GPs- Deliverability of COPING

The secondary outcomes are:

- Response rates of invited practices to participate- Identification of patients at sites- Proportion of identified patients eligible for study inclusion- Participant recruitment uptake through recruitment strategies- Willingness of GPs to be randomised in a main RCT- Assessment of outcome measure to use as the primary outcome in a main RCT- Proportion of participants with repetition of self-harm- Participant attrition, follow-up, and withdrawal rates

This feasibility study is not designed to evaluate health outcome measures formally. We will collect clinical effectiveness data that may support the justification for a future main trial. These data may also be used to decide which outcomes could and should be collected in a future RCT, and to estimate parameters required to calculate the sample size calculation for a fully powered RCT.

The progression decision-making process will include consideration of the feasibility study progression outcomes (aligned to the primary outcomes: see
Table 1) with the study steering committee (SSC), patient and public involvement (PPI) group, and research team to consider if moving to a fully powered RCT is feasible.

**Table 1. T1:** Progression criteria for a future main trial.

Criteria	Go – proceed to RCT	Amend – proceed with minor changes	Stop – do not proceed unless major changes are possible
Consent to study in eligible patients	>30%	15–30%	<15%
Young people participants willing to be randomised in a future RCT	>85%	60–85%	<60%
Fidelity to COPING treatment checklist	>67%	40–67%	<40%
Participant adherence to COPING	>67%	40–67%	<40%
Participant follow-up rate of outcome measures	>80%	50–80%	<50%
Acceptability of COPING to GPs and patients	COPING judged very acceptable by GPs and patients by qualitative data	COPING judged acceptable by GPs and patients by qualitative data	COPING judged somewhat acceptable by GPs and patients by qualitative data
Delivery of COPING by GPs	Delivery of COPING judged strongly feasible by qualitative data	Delivery of COPING judged feasible by qualitative data	Delivery of COPING judged possibly feasible by qualitative data

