### Sample size

Non-randomised COPING delivery:

We will aim to recruit approximately six general practice sites and around 3 GPs at each site. The incidence rate of recorded self-harm in young people in general practice is around 60 per 10,000 person-years
^
23
^. This equates to 60 per 1,000 for the 16–25 age group over one year. If half are eligible for the study (30 per 1,000) and two-thirds of those are identified by our recruiting methods (20 per 1,000) then in a typical GP practice (assumed 6,000 registered patients of which 900 (15%) are in the 16–25 age group) about 18 eligible young people will contact their GP practice per year after self-harm (1.5 eligible young people per practice per month). If six practices are recruited to take part, nine young people would be expected to be eligible per month, and around 104 (the target eligible population size) over about 12 months. From this number (n=104) we would expect to recruit 31 participants (30%) (fulfilling the Go signal for progression for the recruitment criterion – see
Table 1) into the study.

The sample size of n=31 participants is required to test against the feasibility progression criteria (specifically the cut-off for a STOP signal) with at least 90% power, using the normal approximation method for binary outcomes using a 1-sample 1-sided test with 5% alpha (type I error) using the approach of Lewis
*et al.*
^
24
^ In line with the recommendation of the CONSORT-extension for randomised pilot and feasibility studies this provides necessary justification for the sample size requirement for the evaluation of the progression criteria for this feasibility study
^
25
^.

GP survey:

A sample of 100 GPs across England will be surveyed to elicit GP views about a future main RCT of COPING. Achieving 100 GP responses from a convenience sample has recently been shown to be achievable
^
26

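### Paired significance tests of PHQ-9 and SBQ-R in a single-arm study cannot separate a COPING effect from regression to the mean or natural recovery, and should be replaced by labelled estimates of change

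*Protocol article*

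**What the plan says.** The Statistical methods section of the protocol article fixes the analysis of the two clinical scores: "Participant PHQ-9 and SBQ-R scores at baseline and follow-up timepoints will be compared using paired t-test", with a Wilcoxon test if the distribution is not normal. Data collection methods sets the times: "Participant follow-up outcome data collection will be at eight weeks, four, and six months, from baseline". If each follow-up is compared with baseline, that makes up to 2 × 3 = 6 tests.

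Study design states: "This study is a mixed-methods external non-randomised before-after single arm feasibility study". Under Eligibility criteria, patients aged 16–25 qualify if they have self-harmed "in the last 12 months". No PHQ-9 or SBQ-R threshold applies at entry.

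The Outcomes section takes two positions on the clinical data. It says: "This feasibility study is not designed to evaluate health outcome measures formally". The next sentence says: "We will collect clinical effectiveness data that may support the justification for a future main trial". It then names two further uses: choosing outcomes for the main trial, and estimating parameters for its sample size.

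Table 1 lists seven progression criteria: consent, willingness to be randomised, fidelity, adherence, follow-up rate, acceptability and delivery. None concerns the level of, or change in, either score.

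**The concern.** A paired test asks whether the mean score changed. In a single-arm study that change mixes any effect of COPING with two other things. One is regression to the mean, if patients tend to enrol when their scores are above their usual level. The other is natural recovery after an episode. Both push scores in the direction that looks like benefit, and nothing in the design separates them from the intervention.

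The stated uses of the data make this more than a matter of taste. Choosing outcomes and estimating sample-size parameters call for estimates and completeness, not p-values. Only the remaining use, justifying a main trial, could draw on a p-value, and there an uncontrolled p-value is least informative. At stake is how the results are read and what is said in support of the next trial.

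**Working it through.** **1. The plan's own figure.** Sample size says: "The sample size of n=31 participants is required to test against the feasibility progression criteria". It specifies a one-sample, one-sided 5% test, at least 90% power and the normal approximation. Take the adherence and fidelity cut-offs in Table 1 (Stop 40%, Go 67%):

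- n = [(1.645 × √(0.40 × 0.60) + 1.282 × √(0.67 × 0.33)) / 0.27]² = 27.2.
- With continuity correction: (27.2/4) × [1 + √(1 + 2/(27.2 × 0.27))]² = 30.8, so 31.

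The stated 31 reproduces. It rests only on binary progression criteria, so it neither supports the score comparisons nor changes if they are dropped.

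**2. Inputs for the size of the bias.**

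- Pairs: 25, because 80% of 31 is 24.8 and 80% is the Go cut-off for follow-up in Table 1. The case of 31 complete pairs is also shown.
- Test: paired t-test at two-sided 5% (assumed; the article gives no level for these tests). In the direction of improvement the nominal rate is 2.5%.
- Treatment effect: none.
- Shift k: mean baseline lies k SD above the patients' usual level. This is an assumption, shown at 0.25, 0.5 and 1.
- Correlation r between baseline and follow-up: an assumption, shown from 0.5 to 0.8.
- Equal SDs at both times (assumed).

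**3. Formulas.** Expected fall = k(1 − r) SD. SD of change = √(2(1 − r)) SD. Standardised change d = fall / SD of change. The chance of a significant improvement is the upper tail of a noncentral t with n − 1 degrees of freedom and noncentrality d√n, beyond the critical value (2.064 for n = 25; 2.042 for n = 31).

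Example: k = 0.5, r = 0.5, n = 25. Fall = 0.25 SD, SD of change = 1 SD, d = 0.25, noncentrality = 0.25 × 5 = 1.25, chance = 22%.

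**4. Results, chance of a significant improvement per test with no treatment effect.**

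| Shift k | n = 25, r = 0.5 | r = 0.6 | r = 0.7 | r = 0.8 | n = 31, r = 0.5 to 0.8 |
|---|---|---|---|---|---|
| 0 | 2.5% | 2.5% | 2.5% | 2.5% | 2.5% |
| 0.25 SD | 8.7% | 7.7% | 6.8% | 5.7% | 9.9% to 6.3% |
| 0.5 SD | 22.4% | 18.8% | 15.2% | 11.5% | 27.0% to 13.4% |
| 1 SD | 67.0% | 57.4% | 46.0% | 32.9% | 76.9% to 39.9% |

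**5. Several tests.** With no shift at all, six independent tests at 5% would give at least one false positive with probability 1 − 0.95⁶ = 26.5%. The six tests are correlated, so this is a reference value only.

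**The case against.** The best defence has four parts.

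- **The disclaimer is qualified.** The Outcomes section rules out evaluating health outcomes *formally*; it does not say they will not be looked at. An unpowered secondary comparison with no hypothesis, significance level or success rule can coexist with that. This stands in part. A reader might infer a flat contradiction, and the text does not go that far. But a significance test is a formal tool, and it serves neither of the two planning uses.
- **Progression is insulated.** A reader might infer that a significant or non-significant change could tip the Go, Amend or Stop decision. The documents do not support that: no Table 1 criterion uses score change, and the follow-up criterion counts SBQ-R completions out of 93, not scores. This stands in full. The exposed point is the separate sentence on justifying a main trial.
- **The inputs are assumed.** Entry follows an event at any time in 12 months, acute suicide risk needing urgent referral is excluded, and record searches and posters need not catch patients at a peak. The shift may be small. This stands, and is why the 0.25 SD row belongs in the table.
- **The summaries are already there.** A reader might infer that the plan fails to yield SDs for the main sample size. It does not fail: means and SDs (or medians and IQRs) are promised for continuous variables, and a paired t-test cannot be computed without the SD of change. Choosing t-test or Wilcoxon by distribution is conventional, and no harmful consequence of it can be shown here.

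None of this gives an uncontrolled p-value a useful meaning.

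**Conclusion.** The concern holds as a point about interpretation. The plan commits to significance tests of before-after change that cannot distinguish a COPING effect from regression to the mean or natural recovery, and the same article allows the clinical data to support the case for a main trial. The sample size and the formal progression signals are not affected.

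The size cannot be fixed from the documents. With 25 pairs and no treatment effect, the chance of a significant improvement per test is about 6–9%, 12–22% or 33–67% for an assumed baseline shift of 0.25, 0.5 or 1 SD and a correlation of 0.5 to 0.8, against a nominal 2.5%. Any upward shift at entry raises the rate above nominal, and natural recovery would add to it. How far is unknown, so the upper figures are scenarios and not predictions. The change is worth making, but nothing in the study's main purpose depends on it.

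**What to change.** In Statistical methods, replace the paired tests. For each score and follow-up time report the mean (SD), mean change with 95% confidence interval, SD of change, baseline to follow-up correlation and completeness, without p-values. Naming the SD of change and the correlation makes explicit the parameters that the Outcomes section wants for the main trial. The section already reports its progression criteria as estimates with 95% confidence intervals, so this follows its own practice.

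Add a sentence there or under Outcomes: change in PHQ-9 and SBQ-R is uncontrolled and will not be taken as evidence of COPING's effect when the case for a main trial is made. This sentence is essential, because a confidence interval for mean change carries the same bias as the test, and an interval that excludes zero could be misread in the same way.

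The cost is wording, and the loss of a p-value for change. Sample size, schedule and data collection do not change. With 31 complete pairs the interval's half-width would be 2.042/√31 = 0.37 SD of the change score; with 25 pairs, 2.064/√25 = 0.41.

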### Integration of data

Quantitative and qualitative data will be integrated using a triangulation protocol to enhance the validity of findings and assess data complementarity, convergence, and dissonance across key findings
^
34
^.

### Data monitoring and auditing

The CI will manage this study day-to-day and will convene a Study Management Group (SMG) who will be members of the research team to support study delivery. The SMG will be responsible for monitoring study progress and conduct, study protocol implementation, and that the safety and wellbeing of participants is maintained where appropriate. The SMG will escalate any concerns to the SSC and sponsor as required. The CI will meet the SMG at monthly study meetings with communication facilitated by email where needed.

The SSC, which includes an independent statistician, a GP clinical trialist, and a GP researcher, have approved the finalised study protocol, agreed meeting schedules, understand reporting lines to the study sponsor and funder, and agree to the SSC terms of reference. The role of the SSC is to ensure the study is delivered ethically and safely, and to consider the study’s progress in light of new information. The SSC is independent from the sponsor and members have declared no conflicts of interest. The SSC will meet with the CI and some members of the SMG at least once a year. Through the chair of the SSC, the SSC will make recommendations to the CI, SMG, and sponsor, and if early study termination is felt appropriate, the chair will inform the study sponsor.

Authorised representatives of the study sponsor will have access to study data for monitoring and auditing purposes. The CI will conduct audits across the research study following a risk-proportionate approach.

### Harms

The CI will monitor and log all adverse events (AEs) and serious adverse events (SAEs), including their assessment of expectedness (and relatedness where needed), in accordance with the protocol which is in agreement with Keele University Health and Social Care standard operating procedure RM16 Safety Reporting for non-CTIMP research using the study’s CRFs for AEs and SAEs. At site initiation visits, site PIs will be appropriately trained and made aware of this study’s safety reporting requirements. Where a SAE is identified at sites, it must be reported to the study team within 24 hours. Due to the nature of this study, engagement in acts of self-harm from participants during the study is to be expected.

### Ethics and dissemination

This study has received ethics approval from NHS East of England - Cambridge East Research Ethics Committee on 13.11.2023 (23/EE/0238) and Health Research Authority and Health and Care Research Wales Approval on 14.11.2023 (IRAS 327529).

There is risk that participants may describe self-harm or suicidal intent when returning self-report questionnaires or while partaking in an interview. Two risk protocols have been developed. Should likely risk to participants be identified, the relevant risk protocol will be activated, and the participant's GP notified. The protocols outline when breaking confidentiality may be considered. The CI is a GP experienced in assessing risk of self-harm or suicide in patients and all participants will receive a list of free support services for use when needed.

The final full study report will be available from the CI, and findings will be prepared for submission to peer-reviewed journals. All publications, presentations, and correspondence generated will acknowledge NIHR as the funding source. Authorship will be determined in accordance with The International Committee of Medical Journal Editors criteria, and other contributors acknowledged, on manuscripts submitted for peer-reviewed publication.

The results of the study will be available to all stakeholders in ways that are easy to access at no cost. The PPI group will advise on how to best design and disseminate results to the wider public. The findings will also be published on the
COPING study website. Avenues of dissemination include open-access peer-reviewed publications in academic journals, infographics for social media, presentations at clinical, public, and academic conferences, and NHS, NIHR, professional and public networks.

## Discussion

This study will determine the feasibility of conducting a fully powered effectiveness RCT of the COPING intervention in the NHS. The COPING intervention is a novel GP-led intervention that aims to address the intervention evidence gap for young people after self-harm. It was designed through coproduction with patients and GPs and its implementation in usual NHS general practice was considered from the start.

This feasibility study is designed to be pragmatic and deliverable in usual NHS general practice and has been informed by PPI. Three recruitment strategies will be tested to enhance understanding about identifying potentially eligible participants and the study’s progression criteria will determine whether a future main RCT is justified. Qualitative data will provide insights into how to optimise COPING and improve its delivery in practice. A national survey of GPs will provide data to help consider the design of an RCT. The integration of different types of data will enhance the credibility of findings.

The 2023–2028 suicide prevention in England strategy states that a priority area is for tailored support to be available to priority groups
^
35
^. Young people who have self-harmed are a high-risk priority group (encompassing two priority groups: young people and people who have self-harmed) and therefore if acceptable, deliverable, and feasible to be tested in a fully powered RCT, COPING has the potential to benefit patients, GPs, and the NHS, and address this national priority area.

